#### Primary outcome measures

Remission of insomnia, defined using a validated cutoff score on the Insomnia Severity Index (ISI; ISI < 8) [37], is the primary outcome. The ISI is a 7-item self-report questionnaire that assesses the severity of insomnia symptoms over the past 2 weeks, including related functional impairment, and provides a global measure of perceived insomnia severity. The total score ranges from 0 to 28, with higher scores indicating more severe insomnia. The ISI is a well-validated [43] and has demonstrated sensitivity to therapeutic changes [44, 45].

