## Aim 2: To determine the value of the first to second stage CBT-I (OCBT-I or TCBT-I) stepped care model relative to UC for improving insomnia and OSA outcomes after 2nd stage treatment and at 3- and 6-month follow-up

We predict that among participants who did not achieve insomnia remission during the first intervention stage, those assigned to the stepped care TCBT-I group will have the best outcomes. Specifically, we hypothesize that the OCBT-I to TCBT-I group will show significantly greater improvements in insomnia and OSA outcomes compared to the OCBT-I to extended OCBT-I group and compared to non-remitters in the UC group at the end of phase 2 and at follow-up time points (3- and 6-month). To test this hypothesis, linear mixed models (continuous outcomes) across all time points will be utilized, followed by generalized linear models (binary outcomes) at each specific time point. The mixed effects models will include treatment group, time, and group by time predictors, as well as site and its interaction with the other predictors. In order to account for the adaptive nature of the study design in which some subjects receive two treatment modalities and some only one, weighting of records will be employed based on inverse probability weighting (IPW) principles [66].

Power calculations for aim 2 included several considerations. Specifically, based on findings from a previous sequential insomnia treatment study, a second stage of treatment is thought to enhance response rates by about 20% [67]. For the current study, we predict that 5% (UC) and 20% (OCBT-I) of participants will remit after the second stage time frame. If aim 1 expectations are correct, approximately 85% of the 96 UC subjects (*n* = 82) and 65% of the 288 OCBT-I subjects (*n* = 187) will be non-remitters. Further allowing for a 25% attrition by the end of stage 2, these non-responder sample sizes would be 61 (UC) and 140 (OCBT-I). These expected remission percentages and sample sizes yield 83% power to detect differences between groups using an alpha of 5%, based on a 2-proportion *z*-test. Even with IPW methods utilized for adjustment, these calculations suggest adequate power for the comparison.

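### Aim 2 tests remission for two contrasts at three time points without a lead test, and its power statement and exploratory label point to different comparisons

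*Protocol article*

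**What the plan says.** The primary outcome is binary: "Remission of insomnia, defined using a validated cutoff score on the Insomnia Severity Index" (Primary outcome measures). Four places in the article bear on how it is tested in Aim 2.

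- **Objectives and design rationale.** Aim 2 is the stepped-care model against UC, after stage 2 and at 3 and 6 months. Second-stage TCBT-I against second-stage OCBT-I is listed separately, as an exploratory aim.
- **Aim 2, hypothesis.** The TCBT-I group is to show "significantly greater improvements in insomnia and OSA outcomes compared to the OCBT-I to extended OCBT-I group" and also a greater improvement "compared to non-remitters in the UC group". The timing is "at the end of phase 2 and at follow-up time points (3- and 6-month" months).
- **Aim 2, analysis.** Continuous outcomes get a mixed model over all time points. Binary outcomes get "generalized linear models (binary outcomes) at each specific time point".
- **Aim 2, power.** The assumption is "we predict that 5% (UC) and 20% (OCBT-I) of participants will remit after the second stage time frame", with 61 UC and 140 OCBT-I non-remitters after attrition. These figures "yield 83% power to detect differences between groups using an alpha of 5" per cent. The 140 are both second-stage arms together.

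The article gives no other alpha for Aim 2. It names no lead contrast or time point and states no rule for when Aim 2 counts as met.

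**The concern.** Two contrasts at three time points make six separate tests of the primary outcome under one hypothesis. The places listed above do not agree on which of them is confirmatory. The objectives treat one contrast as exploratory, and the hypothesis puts it on the same footing as the other. The power statement covers a comparison that is neither of the two.

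Aim 2 carries the trial's stepped-care conclusion. If the text stays as it is, that conclusion could rest on whichever contrast and visit reaches significance, and neither the 5% nor the 83% would describe it.

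**Working it through.** **1. The stated power.** Pooled two-proportion z-test, two-sided 5%, 61 at 5% against 140 at 20%:

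- pooled proportion = (61 × 0.05 + 140 × 0.20)/201 = 31.05/201 = 0.1545
- SE under no difference = √[0.1545 × 0.8455 × (1/61 + 1/140)] = 0.0554
- SE under the alternative = √[0.05 × 0.95/61 + 0.20 × 0.80/140] = 0.0438
- power = Φ[(0.15 − 1.96 × 0.0554)/0.0438] = Φ(0.943) = 82.7%

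This reproduces the stated 83%. The figure therefore belongs to one two-sided test of the pooled second-stage group against UC.

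**2. The same rates for a hypothesised contrast.** The 1:1 second randomisation splits 140 into about 70 and 70. For TCBT-I alone against UC, 70 against 61:

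- pooled proportion = (3.05 + 14)/131 = 0.1302
- SE under no difference = 0.0589; SE under the alternative = 0.0554
- power = Φ[(0.15 − 1.96 × 0.0589)/0.0554] = Φ(0.623) = 73%

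This is for one visit and takes the pooled 20% as the TCBT-I rate. The article gives no separate rates for the two second-stage arms, so the power of TCBT-I against extended OCBT-I cannot be worked out from it.

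**3. Error if any one of the six tests counts as success.** Independent tests would give 1 − 0.95⁶ = 26.5%, but these tests are correlated. The contrasts share the TCBT-I arm, which gives a correlation of (1/70)/√[(1/70 + 1/70)(1/70 + 1/61)] = 0.48. The same patients are also measured three times. The between-visit correlation is not in the article, so it is an assumption and a range is shown.

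I simulated 40,000 trials per setting with no difference between groups, 70/70/61 patients, remission of 15% or 25%, and a two-sided 5% test each time. Ranges run over the two remission rates.

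| Latent correlation | Correlation of observed remission | Any of six, two-sided | Any of six, favouring TCBT-I | UC contrast only (three tests), two-sided |
|---|---|---|---|---|
| 0.4 | 0.21–0.24 | 24.5–24.7% | 12.6–12.8% | 14.1–14.3% |
| 0.6 | 0.35–0.38 | 23.6% | 12.0% | 13.2–13.9% |
| 0.8 | 0.54–0.57 | 21.0–21.9% | 10.7–10.9% | 11.7–12.9% |
| 0.9 | 0.67–0.70 | 19.7% | 9.9% | 10.9–11.5% |
| 0.95 | 0.77–0.79 | 17.9–18.5% | 9.3% | 10.0–10.8% |

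In the limit of perfect correlation between visits, a normal approximation gives 9.1%, 4.6% and 5.0% for the last three columns. A single two-sided 5% test errs in favour of TCBT-I 2.5% of the time, so 2.5% is the benchmark for the fourth column.

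**4. Error if all six must succeed.** In the same simulations all six tests favoured TCBT-I in under 0.1% of trials, so there is no inflation. Power for such a joint claim cannot exceed that of its weakest component. At the article's rates that is at most the 73% of step 2, not 83%.

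**The case against.** The strongest reply is that the hypothesis joins both comparators and all time points with the word and. Read that way, every component must succeed, no adjustment is needed, and the error for the joint claim stays at or below 5%. This stands as a possible reading: nothing in the article says that one significant result is enough. It does not rescue the plan, because the 83% then describes something other than the hypothesis. Each reading breaks one stated property.

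A second reply is that a testing order is commonly left to the full protocol or analysis plan, neither of which is shown. This is fair, and the absence of an adjustment alone would be no finding. What an unseen document does not remove is the disagreement inside the article between the objectives, the hypothesis and the power statement.

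A reader might infer that Aim 2 carries a false-claim risk of over 20%. The article does not support that as a flat statement:

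- The rate depends on a correlation the article does not give, and falls below 20% at a latent correlation of about 0.9.
- It counts errors in both directions, whereas the hypothesis has one direction.
- It includes a contrast that the objectives call exploratory.
- The any-of-six rule is not stated, and 5% for each test is inferred from the power sentence.

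**Conclusion.** The concern holds as an internal contradiction with a consequence for error or for power, depending on how the hypothesis is read. Aim 2 poses six remission tests without a lead. One of its contrasts is exploratory elsewhere in the article, and its power belongs to a third comparison.

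If any significant test counts, the two-sided familywise error is about 18–25% over latent correlations of 0.4–0.95, and lower as the correlation nears 1. It is about 9–13% in the hypothesised direction, and about 10–14% two-sided with the exploratory contrast left out. If all tests must succeed, error is controlled and the 83% does not apply. The error rates rest on the assumed correlations, on remission of 15–25%, on second-stage arms of 70 and 70, and on a 5% level for each test.

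**What to change.** Reconcile the objectives with the Aim 2 section, and settle the order before the Aim 2 outcome data are analysed:

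1. Name the powered comparison as the single confirmatory Aim 2 test at two-sided 5%: both second-stage arms pooled against UC non-remitters, on remission at the end of stage 2.
2. Treat the 3- and 6-month results for that contrast as secondary, tested in a stated fixed order and only if the first test succeeds.
3. Report TCBT-I against extended OCBT-I as exploratory, as the objectives already say, with estimates and 95% confidence intervals. Reword the Aim 2 hypothesis to match.

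This takes a few lines of text and no new data. The lead test keeps its full 5% and its 83% power. By comparison, a Bonferroni split over six tests (0.05/6 = 0.0083) would leave that comparison with about 53%. The small cost is that follow-up results cannot be claimed if the first test fails.

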## Methods

### Study design and setting

This study is employing a Sequential Multiple Assignment Randomized Trial (SMART) design to test value added of providing a therapist-directed CBT-I as a second stage treatment to those who do not initially achieve acceptable outcomes with OCBT-I. Eligible patients are being randomly assigned in a 3:1 ratio to an online (OCBT-I) program (Sleepio^TM^) combined with usual PAP care or to a usual PAP care (UC) only condition. All eligible patients receive sleep hygiene education at their baseline assessment. Eight weeks after randomization, patients randomized to OCBT-I who meet study criteria for remission, defined as a score of less than 8 on the Insomnia Severity Index [37], will receive no further insomnia treatment and those who do not meet remission criteria are randomized again in a 1:1 ratio to a 2nd-stage intervention consisting of either therapist-lead CBT-I (TCBT-I) or continued, extended access to the OCBT-I resources. All participants complete all study outcome measures at baseline and several time points post-randomizations (8 weeks, 16 weeks, 3 months, and 6 months; see Figs. 1 and 2). Those assigned to the UC condition are offered CBT-I (choosing either OCBT-I or TCBT-I) at the end of the study period.

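### The 83% power stated for Aim 2 is right for both second-stage arms pooled against UC, but it does not describe the two TCBT-I contrasts that the Aim 2 hypothesis names

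*Protocol article*

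**What the plan says.** All references are to the protocol article.

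- **Aim 2 heading, and the same aim under Objectives and design rationale:** the value of the stepped-care model, with either OCBT-I or TCBT-I as second stage, relative to UC.
- **Aim 2 hypothesis:** "the OCBT-I to TCBT-I group will show significantly greater improvements in insomnia and OSA outcomes compared to the OCBT-I to extended OCBT-I group", and also compared with non-remitters in the UC group, at the end of the second stage and at follow-up.
- **Aim 2 power:** "we predict that 5% (UC) and 20% (OCBT-I) of participants will remit after the second stage time frame". The section expects 82 UC non-remitters and that "65% of the 288 OCBT-I subjects (*n* = 187) will be non-remitters". After 25% attrition it uses 61 UC and 140 OCBT-I patients. Then: "These expected remission percentages and sample sizes yield 83% power to detect differences between groups using an alpha of 5" per cent, "based on a 2-proportion *z*-test". The paragraph closes by calling power adequate for the comparison even with inverse probability weighting (IPW).
- **Study design and setting:** of the OCBT-I patients, "those who do not meet remission criteria are randomized again in a 1:1 ratio to a 2nd-stage intervention", either TCBT-I or extended OCBT-I.
- **Objectives and design rationale:** TCBT-I versus second-stage OCBT-I is listed as an exploratory aim, separate from Aim 2.

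**The concern.** The power paragraph follows directly on a hypothesis about TCBT-I alone, yet its sample size of 140 is the whole OCBT-I non-remitter group before the second randomisation is taken into account. A reader will naturally attach the 83% to the hypothesis just stated. The TCBT-I arm has half those patients, and the article gives no remission rate that separates TCBT-I from extended OCBT-I.

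What is at stake is interpretation. The Discussion presents the trial as a test of the value added by therapist-directed CBT-I. If TCBT-I versus extended OCBT-I comes out null and the reader believes that contrast had 83% power, the result may be taken as evidence that a therapist adds nothing, when the data may simply be too few to tell.

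**Working it through.** **Inputs (Aim 2 section unless noted).** Second-stage remission: UC 5%, OCBT-I 20%. Analysed non-remitters: UC 82 × 0.75 = 61.5, stated as 61; OCBT-I 187 × 0.75 = 140.25, stated as 140. Second-stage allocation 1:1 (Study design and setting), so 140/2 = 70 per arm. Alpha is 5%; sidedness is not stated, and two-sided reproduces the stated figure.

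**Formula.** Two-proportion z-test with pooled variance under the null:

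power = Φ{(|p₁ − p₂| − 1.96·s₀)/s₁}, where
- s₀ = √[p̄(1 − p̄)(1/n₁ + 1/n₂)], with p̄ the weighted mean rate;
- s₁ = √[p₁(1 − p₁)/n₁ + p₂(1 − p₂)/n₂].

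**Step 1: the article's figure.** UC 61 at 5%, OCBT-I 140 at 20%. p̄ = (61 × 0.05 + 140 × 0.20)/201 = 0.1545; s₀ = 0.0555; s₁ = 0.0438. Power = Φ{(0.15 − 1.96 × 0.0555)/0.0438} = Φ(0.94) = 82.7%. The stated 83% is reproduced, with all 140 in one group.

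**Step 2: TCBT-I alone versus UC.** 70 versus 61, same formula. At 20% versus 5%: p̄ = 0.1302; s₀ = 0.0589; s₁ = 0.0554; power = Φ(0.62) = 73.3%. The article does not say what TCBT-I alone will achieve, so a range is needed:

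| TCBT-I rate (UC 5%) | Power, 70 vs 61 |
|---|---|
| 20% | 73% |
| 22.5% | 83% |
| 25% | 90% |

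The 20% row depends somewhat on the test: Fisher's exact test gives 71%, the unpooled z-test 77%. If alpha were halved to 2.5% to cover two contrasts, that row falls to 63%.

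**Step 3: TCBT-I versus extended OCBT-I.** 70 versus 70. Every rate pair here is an assumption.

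| TCBT-I | Extended OCBT-I | Gap (points) | Power |
|---|---|---|---|
| 20% | 15% | 5 | 12% |
| 20% | 10% | 10 | 38% |
| 25% | 15% | 10 | 31% |
| 20% | 5% | 15 | 77% |
| 28.5% | 10% | 18.5 | 80% |
| 35% | 15% | 20 | 79% |
| 35.4% | 15% | 20.4 | 80% |
| 30% | 10% | 20 | 85% |

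With extended OCBT-I at 10% to 15%, 80% power needs a gap of about 19 to 20 points. For scale, the article expects 20% − 5% = 15 points between second-stage CBT-I and UC. A smaller gap comes close only if extended OCBT-I does no better than UC (20% versus 5%, 77%). None of these figures allows for IPW or multiplicity.

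**The case against.** The strongest reply is that nothing is miscalculated. The 83% is correct, it answers Aim 2 as titled, the two groups are labelled UC and OCBT-I, and the closing sentence speaks of one comparison. All of that stands: this is a mismatch between the hypothesis and its power statement, not an arithmetic error.

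A reader might infer that the article claims adequate power for the TCBT-I contrasts. It does not do so by name; the adequacy sentence follows the pooled calculation. The fault is that nothing tells the reader that the hypothesis above it is not covered.

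Second, an exploratory contrast need not have 80% power, and the objectives call TCBT-I versus second-stage OCBT-I exploratory. That is fair, but the Aim 2 section makes the same contrast part of its hypothesis and predicts a significant difference. TCBT-I versus UC is not called exploratory anywhere.

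Third, it is tempting to say flatly that the trial has 73% power against UC and far less against extended OCBT-I. The documents do not support either as a fixed statement. The 73% requires TCBT-I to remit at exactly 20%; if 20% is the average of the two arms and TCBT-I is the better, its power against UC is higher. Against extended OCBT-I, power runs from 12% to 85% over the assumed pairs above.

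Fourth, the hypothesis is tested first with linear mixed models on continuous outcomes. A simple comparison at one time point with 70 per arm has 80% power for about 2.80 × √(2/70) = 0.47 SD, a moderate difference. So one cannot say that the trial could detect only very large effects; the 19 to 20 points apply to binary remission.

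**Conclusion.** The point holds as a mismatch. The 83% belongs to all OCBT-I non-remitters pooled versus UC (140 versus 61, 20% versus 5%) and to the Aim 2 heading; it does not carry over to TCBT-I alone, which has about 70 patients.

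- **TCBT-I versus UC:** below the stated figure (73%) if TCBT-I remits at 20%, the only active rate given; level with it at 22.5%; above it at 25%.
- **TCBT-I versus extended OCBT-I:** power cannot be fixed from the article. On binary remission it falls well short of 80% for gaps of 5 to 10 points, and reaches 80% at about 19 to 20 points if extended OCBT-I remits at 10% to 15%.

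These results rest on a two-sided 5% pooled z-test, an even split of the 140, and no allowance for IPW or multiplicity. Separately, the objectives and the Aim 2 section disagree on whether TCBT-I versus second-stage OCBT-I is exploratory.

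**What to change.** 1. State in the Aim 2 power paragraph that the 83%, and the statement that power is adequate, refer only to pooled second-stage CBT-I versus UC (140 versus 61, 20% versus 5%).
2. Add, with its condition: TCBT-I alone versus UC (about 70 versus 61) has about 73% power if TCBT-I remits at 20%, 83% at 22.5% and 90% at 25%, against UC at 5%.
3. Add: TCBT-I versus extended OCBT-I (about 70 per arm) reaches 80% power on binary remission for a gap of about 19 to 20 points, for example 28.5% versus 10% or 35.4% versus 15%. Say that these rates are assumptions and that IPW and multiplicity are not included.
4. Give TCBT-I versus second-stage OCBT-I one status in both the objectives and the Aim 2 hypothesis. If it is exploratory, take it out of the hypothesis. If it is an Aim 2 hypothesis, give its power with assumed rates for each arm. Either way, report it as an estimate with a confidence interval, so that a null result is not read as no added value of a therapist.

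The cost is a less favourable stated figure. The recruitment period ended on 30 June 2022 and the change needs no extra patients.

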## Discussion/conclusions

OSA and chronic insomnia are prevalent and debilitating conditions, with the common co-occurrence of these disorders amplifying morbidity and complicating the management of affected patients. Unfortunately, previous research provides limited guidance as to what constitutes the best and most practical management approach for this comorbid patient group. Some studies show that when CBT-I and standard OSA therapies are combined, outcomes are markedly improved over those seen with OSA therapies alone [24, 25]. However, a dearth of trained providers available to deliver CBT-I has long served as a pragmatic barrier to the widespread use of this therapy in clinical practice [68]. The emergence of sophisticated OCBT-I programs could improve access. OCBT-I studies have shown promising results for individuals with insomnia [30, 32, 69–72]. The efficacy of OCBT-I for individuals with comorbid insomnia/OSA is relatively unknown. Nonetheless, given the putative scalability and apparent efficacy of this intervention approach, OCBT-I could represent a first stage intervention in a broader stepped care model that allocates more intensive and less assessable therapist-delivered CBT-I only to those who show an inadequate response to lower intensity OCBT-I [36]. However, the efficacy of OCBT-I as a first stage therapy within a broader stepped care management strategy has yet to be tested with comorbid OSA/insomnia patients.

To date, no large, well-controlled trials with adequate follow-up periods have been conducted to ascertain optimal sleep/wake symptom management strategies for comorbid OSA/insomnia patients. This study offers the first trial of this nature, which includes a number of innovative features, including testing an OCBT-I program used in conjunction with PAP as a first stage intervention for patients with comorbid OSA/insomnia. Furthermore, determining the types of patients that comprise these first stage responders will help inform future treatment decisions in clinical settings. The stepped care, “SMART” clinical trial design will uniquely test whether there is “value added” of providing therapist-directed CBT-I to those who do not initially achieve acceptable outcomes with OCBT-I. Ascertaining the best deployment of online and therapist delivered CBT-I resources for comorbid OSA/insomnia patients, as well as investigating if certain patient characteristics predict treatment preferences and responses, will serve to inform future clinical decision making processes.

### Trial status

Protocol Version 2, 25 March 2020; recruitment period is from April 15, 2017, to June 30, 2022. This manuscript was initiated in 2019. Due to the multi-site nature of the study, the number of contributing authors, the many responsibilities of the involved parties, and the impact of COVID-19, the draft cycled through several rounds of edits, which took longer than expected due to these circumstances. The manuscript was approved by all co-authors for submission in August 2021. However, SPIRIT requirements were not met and the entire draft had to be reworked. During this year, some of the key authors’ had unforeseen extended medical leave, slowing these revisions. Finally, when this SPIRIT revised version uploaded for submission on June 17, 2022, additional institutional documentation was required, delaying the complete manuscript submission to July 18, 2022, after recruitment was completed.

## Data Availability

Data sharing is not applicable to this article as no datasets were generated or analyzed for the current manuscript. However, once all final study analyses for the current trial are completed, the study PIs will consider any reasonable requests to supply any de-identified data to support the protocol. Additionally, study PIs will consider any reasonable requests for de-identified study datasets, once analyses are complete, and statistical codes. The full study protocol is available upon reasonable request.
